## **Medical History**

A medical history and demographic information will be collected on all patients during the Selection and Imaging period. The history will include details regarding all past and current illnesses, past surgical/medical procedures, and concomitant medication usage. Allergies and potential past/recent adverse drug reactions will also be reviewed. Details regarding cardiovascular risk factors and habits, including smoking and alcohol use, nutrition, physical activity, and quality of life will be collected at least during the Imaging Period. Demographic information including age, race, gender, height, and weight will be collected on all patients during this period.

## **Physical Examination**

A targeted physical examination will be performed in the Selection period. The examination will include vital signs: blood pressure and pulse. A targeted physical examination (heart, lungs, and extremities) will be performed at screening. Vital signs will be obtained immediately prior to MSCT scanning and will be repeated just after scanning. Vital signs will be monitored during/following MSCT if beta-blockers are given per local standards. The patient will also be observed for at least 2 days after study-related procedures for any new clinical signs and complications.

## **Electrocardiography**

A standard 12-lead ECG will be performed within 2 days prior to the MSCT. This is reviewed prior to inclusion to ensure no ECG-related exclusion criterion is present. In addition, after the patient has been placed on the ECG in the CT scanner room, the rhythm will again be reviewed prior to imaging.

## **Baseline Laboratory Tests**

Blood will be obtained either at the time of laboratory testing, MSCT (during IV placement) or at the time of cardiac catheterization, for cholesterol profile and serum biomarkers. A locally accepted/certified clinical pathology laboratory will perform the blood and urine tests specified by the protocol within 24 hours before CT. Serum chemistry profile will have to include BUN, creatinine, glucose, sodium, potassium, chloride and bicarbonate. If appropriate, a pregnancy test must also be performed. A qualifying serum creatinine must be performed immediately (maximum of 24 hours) before MSCT.

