## **9 Assessment of Safety**

### **Adverse Events Monitoring for MSCT**

Safety monitoring of the MSCT examination (and if performed MRI) will be performed. This will include monitoring of adverse events possibly related to study-related procedures; such as CT contrast administration, radiation exposure, and medications used for the MSCT (such as beta-blockers and nitroglycerine). Clinical laboratory tests (e.g., creatinine) will be reviewed. Assessment of allergic reactions will be performed.

The safety profile and known side effects and expected adverse events related to contrast media have been well described in the literature. Known and anticipated events include, but are not limited to, allergic reaction (mild or severe), anaphylaxis, pruritus, rash, renal impairment, renal failure, contrast-induced nephropathy, vasovagal reaction. Known risks of intravenous line placement include bleeding, infection, tissue or nerve injury, and vasovagal reaction. Known risks related to beta-blocker medication include, but are not limited to, hypotension, bradyarrhythmia, allergic reaction, bronchospasm, and precipitation of reactive airway disease, heart block. Known risks of nitroglycerine use include headache, reduction in blood pressure, hypotension. These rare but important potential adverse events will be monitored at each site using the corresponding CRFs.

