### **Laboratory Test Results**

All laboratory values must be reviewed and appraised by the investigator or research personnel for clinical significance. For any abnormal laboratory value considered to be new since baseline and clinically significant, details must be provided on the Laboratory Adverse Event case report form. This will include whether the event is considered serious, the relationship to the MSCT or MRI contrast agent or other agents, the action taken, and patient outcome. Significant abnormal values occurring during the study are to be followed until repeat values return to normal, stabilize, or are no longer considered clinically significant.

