## **13 Ethics**

### **General**

The study will be conducted in accordance with the protocol, the current revision of the Declaration of Helsinki, the current guideline for Good Clinical Practice, and with the applicable regulatory requirements. The study protocol will have to be approved by the institutional review boards of each participating center. MSCT exposes the patients to a radiation dose of approximately 15 to 20 mSv. To ensure adherence to legal regulations and safety of the patients, the Federal Department for Radiation Protection will review the study protocol. Iodinated contrast agents will be used for MSCT. These agents have a well-known low risk profile (30). However, these agents will be administered twice for MSCT. Patients will benefit from the detection of noncoronary causes of their symptoms by MSCT.

Due to the importance of protecting study data at the Charité, access to all computer files and programs will be restricted to authorized personnel through the use of passwords and automatic access control at the file level. The Charité intranet has the latest firewall protection and the latest MacAfee virus protection, both of which are updated daily.

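### The Protocol commits to monitoring contrast-related renal harm from MSCT but schedules creatinine only before it, so symptomless injury is not systematically measured and a later rise cannot be assigned to either test

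*Protocol*

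**What the plan says.** Section 6, Baseline Laboratory Tests, fixes the timing of the chemistry. It places the "blood and urine tests specified by the protocol within 24 hours before CT", lists creatinine and BUN in the serum profile, and adds that "A qualifying serum creatinine must be performed immediately (maximum of 24 hours) before MSCT". The same section allows one blood sample to be taken on any of three occasions, the last being "at the time of cardiac catheterization, for cholesterol profile and serum biomarkers". Creatinine is not named for that sample.

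Section 9, Adverse Events Monitoring for MSCT, lists "renal impairment, renal failure, contrast-induced nephropathy" among the anticipated effects of contrast media. It says that "Clinical laboratory tests (e.g., creatinine) will be reviewed" and closes with "These rare but important potential adverse events will be monitored at each site using the corresponding CRFs". Section 9, Laboratory Test Results, gives the reporting rule: "For any abnormal laboratory value considered to be new since baseline and clinically significant", details go on a dedicated form, including the relation to the contrast agent.

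On exposure, section 7 (Contrast Agent) gives about 50 to 70 ml for each of two CT studies. Section 13 (General) calls the risk of these agents low and then adds: "However, these agents will be administered twice for MSCT". Section 12 (Methods Against Bias) sends every patient on to conventional angiography. Section 13 (Time Intervals between Procedures) allows up to 14 days for this and sets no minimum.

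**The concern.** A rule that compares a value with baseline needs a second value, and a rule that asks which contrast exposure caused a change needs a value between the exposures. The Protocol schedules neither for creatinine. Contrast-related renal injury can occur without symptoms, and such cases come to light only if creatinine is measured.

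What is at stake is the renal part of the safety report. If few or no renal events are recorded after MSCT, the reader cannot tell whether they did not occur or were not looked for. If a raised creatinine turns up in routine care after both procedures, the form asks for an attribution that the data cannot support. An analysis plan cannot repair this later, because a sample that was not taken cannot be recovered.

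**Working it through.** The Protocol states no figure for this point, so the check sets what section 9 requires against what is scheduled.

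**Creatinine time points scheduled**

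| Window | Scheduled | Source |
|---|---|---|
| Within 24 hours before MSCT | 1 | Section 6, Baseline Laboratory Tests |
| Between MSCT and angiography | 0 | No section names one |
| After angiography | 0 | No section names one |

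**Time points the section 9 rules need**

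- To call a value new against baseline: at least 1 value after exposure. Scheduled: 0 + 0 = 0.
- To separate CT contrast from angiographic contrast: at least 1 value between the two. Scheduled: 0.

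**What follows MSCT instead.** Section 6 (Physical Examination) and section 7 (Scanning and Reconstruction) provide vital signs and at least 2 days of observation or local-standard monitoring for complications. Neither names a laboratory test.

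**Exposure before angiography.** Two CT injections give 2 × 50 = 100 ml to 2 × 70 = 140 ml. Angiography adds a further contrast exposure. Its volume is not given, but secondary objective 9 in section 4 compares contrast amounts between the two tests.

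**Interval.** The gap from MSCT to angiography runs from no stated minimum up to 14 days, and section 5 (Study Design) expects the imaging period to last under 1 week. Angiography may therefore fall inside the 2-day observation after MSCT, and in that case clinical observation does not separate the two exposures either.

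**Is the baseline itself sound?** Yes. The chemistry profile and the qualifying creatinine both precede MSCT. Only the lipid and biomarker sample may be drawn later, and section 9 does not name it as a renal safety test.

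**The case against.** The strongest reply is that the Protocol does not limit monitoring to clinical signs. The 2-day period after MSCT follows local standard, which may include a creatinine. The section on laboratory results requires significant abnormal values arising during the study to be followed up, which presupposes that some values are obtained. The case report forms and the MSCT procedure (Appendices 1 and 2) are not shown and may contain a repeat measurement. A section on baseline tests is also not where one would look for a follow-up draw. All of this stands, and it limits the point: overt renal failure or a locally measured rise could be captured. It does not remove the mismatch, because no section of the Protocol schedules or refers to a creatinine after contrast, and capture by local habit is not systematic.

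A reader might infer four stronger claims, which the documents do not support:

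- **That the comparison of complications in secondary objective 6 is invalid.** Renal harm is not on that list. It could enter only as another complication that prolongs hospital stay by at least 24 hours, and a symptomless rise would not by itself meet that condition.
- **That the gap favours MSCT.** Scheduled creatinine after exposure is absent for both tests (0 and 0), so no direction of bias follows.
- **That the baseline may be taken after MSCT.** This is true only of the lipid and biomarker sample, not of creatinine.
- **That renal injury is undetectable in all 90 patients.** The routes just described rule out so broad a statement.

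**Conclusion.** The point holds as a mismatch between section 6 (Baseline Laboratory Tests) and section 9. The Protocol promises renal monitoring and sets a baseline-referenced, attributed reporting rule, but schedules creatinine at one time point before MSCT and at none afterwards. Symptomless renal injury is not systematically measured, and a later rise cannot be assigned to the CT injections or to angiography.

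The size can be stated only as this count and as the 100 to 140 ml of CT contrast given before angiography. The Protocol gives no renal event rate, so the number of missed events cannot be estimated. The primary accuracy endpoint is not affected.

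The conclusion assumes that the appendices do not already require a creatinine after MSCT. If they do, the Protocol text should say so and the point reduces to a cross-reference.

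**What to change.** Reconcile Baseline Laboratory Tests with the two section 9 passages and with Time Intervals between Procedures. Either of two routes would do.

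1. **Collect the value.** For every patient, record a creatinine from blood taken at catheterisation before angiographic contrast, and enter it as the post-MSCT value. Record the time since MSCT and flag values taken early. The catheterisation draw has to be stated as applying to everyone, because at present it is only one of three options for the lipid and biomarker sample. If renal events are to be compared between the two tests, ascertainment after angiography must be equally systematic; relying on whatever routine value exists would measure one test by design and the other by chance.
2. **Limit the claim.** If no value is added, state that laboratory-defined renal events were not systematically assessed, and draw no conclusion on renal safety.

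The first route costs one added analyte, one case report form field, and a small extra draw for patients whose lipid and biomarker sample was taken earlier. Its main weakness is low sensitivity when angiography follows MSCT closely, which is why the interval must be recorded. The second route costs nothing in conduct but gives up any renal safety statement. Both concern data collection and reporting only; no creatinine limit, contrast rule or treatment decision is proposed.

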**Further Baseline Tests**

Standard two-dimensional transthoracic echocardiography is encouraged as a baseline examination but is not a condition for participation. The results of tests for detection of myocardial ischemia will be recorded using CRFs (see Appendix 1) but will also not be a requirement for participation.

## 7 MSCT

MSCT coronary angiography is to be performed within 14 days after inclusion of patients for safety reasons. In no instance this time period is allowed to be delayed. Also for safety reasons and reliable comparability of the two tests the time between MSCT and conventional coronary angiography should not be longer than 14 days.

### MSCT

All inclusion/exclusion criteria will be reviewed again just prior to the MSCT. Each participant will be clinically evaluated briefly before and following imaging.

### Preparation

Patients will be instructed to lay still on the examination table and to hold the breath after instruction (inspiration instruction) for the required period. Valsalva maneuvers should be avoided by breathing in only to a maximum of 80% of the entire capacity. An ECG will be placed on the anterior hemithorax to allow retrospective gating of the images to the ECG tracing.

Nitroglycerine (glycerol trinitrate, 0.8 mg glycerol trinitrate [nitroglycerine], Nitrolingual N Spray, Pohl-Boskamp) shall be given sublingually prior to MSCT coronary angiography as recently described (19) if no contraindications to nitroglycerine are present (severe aortic stenosis, hypertrophic obstructive cardiomyopathy, intake of inhibitors of phosphodiesterase within the last 24 hours, e.g. sildenafil, and severe hypotension, i.e. systolic blood pressure below 100 mm Hg). In patients with contraindications to nitroglycerine MSCT will be conducted without nitroglycerine and the patients will not be excluded from the trial. Patients on chronic therapy with oral or topical long acting nitrates may and should continue their regular use.

Patients were instructed to avoid caffeine and black tea prior to scanning. Patients on beta blockers should continue them during the study. Additional intravenous and/or oral beta blockers (according to the MSCT SOP) may be given prior to the MSCT in order to reduce heart rate to  $\leq$  65 beats per minute during scanning. Betablocker and nitroglycerine administration will be performed according to the SOP for performance of MSCT (see Appendix 2). Atenolol (50-150 mg) is recommended as the oral beta blocker approximately 1 hour prior to MSCT in patients with a resting heart rate during the physical examination of at least 65 beats per minute. In patients with a resting heart rate of at least 60 immediately prior to CT scanning on the examination table further intravenous beta blockers (recommendation: Esmolol [Brevibloc] at a

---

maximum dose of 600 mg, maximum of 10-30 mg per minute) can be given.

Patients on metformin or other metformin-containing agents may participate in the study. The patient's clinical physician or site should follow their local standard of care in regards to discontinuation/re-initiation of metformin when intravenous contrast agent administration is planned to be administered. It is generally encouraged that patients with an increased creatinine level (above 1.5 mg/dl) stop their metformin for 2 days following contrast injection (according to the ESUR guideline).

Patients with known allergoid reactions to iodinated contrast agents shall undergo premedication according to local guidelines.

### **Scanning**

CT scanning will be performed on 320-slice scanner with the patient in supine position and holding his or her breath in submaximum inspiratory position. Patients will be positioned off-center to the right to place the heart in the center of the scan field. Electrocardiogram leads will be positioned outside the scan range and arms were placed above the head to improve image quality. The 320-mm scan field-of view (M) of the CT scanner will be used for image acquisition. First, an anteroposterior scanogram (120 kv, 50 mA) will be obtained for further planning. Based on the dimensions of the heart on this scanogram the scan length of the subsequent CT coronary angiography will be defined.

### **Contrast Agent**

MSCT requires contrast agent injection into an antecubital vein (Iomeron, 400 mg/ml, Bracco). An intravenous line will be placed for the administration of the contrast agent. This will be preferably an 18 or 20 gauge intravenous line placed in the right arm. Approximately 50-70 ml of an intravenous contrast will be administered during each of the two CT studies (coronary arteries by CTA and myocardial perfusion by CTP). The flow of the contrast agent will be 5 ml/s with the exception of patients with a body weight of <60 kg – these patients will receive the intravenous contrast agent with a flow rate of 4 ml/s. A region of interest in the aorta will be used to track contrast agent transit time. An automated breathhold command ("breathe in and hold your breath", 4-sec breathhold) will be given when an absolute increase of 200 Hounsfield units in the descending aorta after contrast agent injection had been detected with the automatic sure-start option of the scanner. The contrast agent will be injected in two phases: the first phase will be 50-70 ml of contrast and the second phase will be 40 ml of saline. This will be

administered through an automated power injector following a saline injection (biphasic) in a standardized fashion.

### **Scanning and Reconstruction**

The stationary prospectively triggered scan of the coronary arteries shall cover the range from approximately 1 cm above the left atrium to the base of the heart. In addition, a single axial slice will be acquired at the largest diameter of the heart, which served to define the reconstruction field-of view to be used for all subsequent reconstructions. The size of this field-of view will be in the range of 180 to 220 mm in order to achieve an in-plane pixel size of approximately  $0.4 \times 0.4 \text{ mm}^2$  at an image matrix of 512 by 512. The reconstruction field-of view will be set to cover the entire heart and the descending aorta and will be used for CT coronary angiography. All MSCT scans will be performed at 0.5 mm detector collimation. The reconstructed slice thickness will be allowed to be 0.5 mm while the reconstruction interval will be allowed to be between 0.4 and 0.5 mm. The reconstructed FOV (round) shall be set at a maximum of 220 mm and a minimum of 180 mm in size. At the time of the MSCT, the images of the lungs and mediastinum (at large FOV, at least 320 mm) with a maximum reconstructed slice thickness of 5 mm (recommendation: 3-5 mm) will be immediately reviewed at the site for non-cardiac findings according to the MSCT SOP. The Radiology investigators will report these non-cardiac findings to the patient's clinical physician and to the patient in a timely fashion to immediately direct further necessary management.

For CTP imaging patients will receive adenosine at a standard dose ( $140 \mu\text{g/kg/min}$ ) through an intravenous line in the antecubital fossa of the left arm at least 20 min after nitroglycerin for CTA. Stress CTP will be performed 4:30 min after initiation of the continuous adenosine infusion.

Following the MSCT study, the patient will be monitored per local standard for at least 2 days to identify procedural complications. At least one post-MSCT set of vital signs will be obtained. The IV line will then be removed after the patient has been felt to have been adequately monitored.

### **Other Information**

If the patient has had an interim change in cardiac clinical status (e.g. worsening of symptoms requiring immediate catheterization without CT), then the patient will be excluded from the analysis.

The MSCT raw data and reconstructed data will be saved at each site for at least 30 years after completion of the study.

### **Non-cardiac Findings on MSCT**

MSCT during the course of this study is being performed for the purpose of coronary artery imaging and assessment of myocardial perfusion. Partially inclusive in these studies will be images of non-coronary structures. Although the CT performed for purpose of this study is performed to optimize coronary and myocardial imaging primarily, other structures will be visualized and should be interpreted. These interpretations should be made with the understanding that they are likely limited by the technique used specifically for the study. The CT images shall be reviewed immediately by a radiologist. Interpretations of the non-cardiac structures should be communicated with the patient, patient's physician, primary care physician, or other pertinent health care provider. Immediate communication is important in the view of potential significantly abnormal or concerning findings. In addition, the findings will be noted on the MSCT CRFs. It is the Radiology investigators who are responsible for the appropriate reading and communications of these non-cardiac CT findings.

## **8 Assessment of Efficacy**

### **Primary Efficacy Endpoints**

The hypothesis of the present trial will be that for combined CTA and CTP the per-patient diagnostic accuracy of 320-slice CT is significantly greater than 75% at an expected per-patient diagnostic accuracy of 87%.

### **Secondary Efficacy Endpoints**

Diagnostic accuracy on other levels (e.g. per-stent) will be conducted. Image quality will be analyzed as well as patient acceptance, cost-effectiveness, non-coronary findings, and radiation dose. Also procedural complications of the two tests will be compared.

## **9 Assessment of Safety**

### **Adverse Events Monitoring for MSCT**

Safety monitoring of the MSCT examination (and if performed MRI) will be performed. This will include monitoring of adverse events possibly related to study-related procedures; such as CT contrast administration, radiation exposure, and medications used for the MSCT (such as beta-blockers and nitroglycerine). Clinical laboratory tests (e.g., creatinine) will be reviewed. Assessment of allergic reactions will be performed.

The safety profile and known side effects and expected adverse events related to contrast media have been well described in the literature. Known and anticipated events include, but are not limited to, allergic reaction (mild or severe), anaphylaxis, pruritus, rash, renal impairment, renal failure, contrast-induced nephropathy, vasovagal reaction. Known risks of intravenous line placement include bleeding, infection, tissue or nerve injury, and vasovagal reaction. Known risks related to beta-blocker medication include, but are not limited to, hypotension, bradyarrhythmia, allergic reaction, bronchospasm, and precipitation of reactive airway disease, heart block. Known risks of nitroglycerine use include headache, reduction in blood pressure, hypotension. These rare but important potential adverse events will be monitored at each site using the corresponding CRFs.

